# Value of ultra-high field MRI in patients with suspected focal epilepsy and negative 3 T MRI (EpiUltraStudy): protocol for a prospective, longitudinal therapeutic study

**DOI:** 10.1007/s00234-021-02884-8

**Published:** 2022-01-05

**Keywords:** Epilepsy, Epilepsy surgery, UHF MRI, 7 T, 9.4 T

## Abstract

**Purpose:**

Resective epilepsy surgery is a well-established, evidence-based treatment option in patients with drug-resistant focal epilepsy. A major predictive factor of good surgical outcome is visualization and delineation of a potential epileptogenic lesion by MRI. However, frequently, these lesions are subtle and may escape detection by conventional MRI (≤ 3 T).

**Methods:**

We present the EpiUltraStudy protocol to address the hypothesis that application of ultra-high field (UHF) MRI increases the rate of detection of structural lesions and functional brain aberrances in patients with drug-resistant focal epilepsy who are candidates for resective epilepsy surgery. Additionally, therapeutic gain will be addressed, testing whether increased lesion detection and tailored resections result in higher rates of seizure freedom 1 year after epilepsy surgery. Sixty patients enroll the study according to the following inclusion criteria: aged ≥ 12 years, diagnosed with drug-resistant focal epilepsy with a suspected epileptogenic focus, negative conventional 3 T MRI during pre-surgical work-up.

**Results:**

All patients will be evaluated by 7 T MRI; ten patients will undergo an additional 9.4 T MRI exam. Images will be evaluated independently by two neuroradiologists and a neurologist or neurosurgeon. Clinical and UHF MRI will be discussed in the multidisciplinary epilepsy surgery conference. Demographic and epilepsy characteristics, along with postoperative seizure outcome and histopathological evaluation, will be recorded.

**Conclusion:**

This protocol was reviewed and approved by the local Institutional Review Board and complies with the Declaration of Helsinki and principles of Good Clinical Practice. Results will be submitted to international peer-reviewed journals and presented at international conferences.

**Trial registration number:**

www.trialregister.nl: NTR7536.

## Introduction

About 30–40% of patients with epilepsy are drug-resistant, with higher rates for children [1]. Resective epilepsy surgery is a well-established, evidence-based, treatment option for 10–50% of drug-resistant patients, depending on the underlying etiology [2–4]. One of the major predictive factors for good surgical outcome (i.e., seizure freedom) is the detection of a potential epileptogenic lesion/zone on magnetic resonance imaging (MRI) [5–7]. Approximately 30% of adult and pediatric patients with focal epilepsy have no identifiable, potential epileptogenic lesion on MRI, “MRI-negative” [8–10]. Consequently, a considerable number of MRI-negative drug-resistant patients are not eligible for resective surgery, leading to continuation of disease burden and lower quality of life [9].

Recent developments in the field of non-invasive preoperative examinations, like high-density electroencephalography (EEG), EEG-functional MRI (fMRI), single photon emission computed tomography (SPECT), positron emission tomography (PET), magnetoencephalography (MEG), and ultra-high field (UHF) MRI, have improved localization of the epileptogenic zone, leading to surgical treatment in patients who previously were not considered candidates for epilepsy surgery [11–13]. The detection rate of potential epileptogenic lesions on MRI is strongly dependent on technical factors, such as magnetic field strength (in tesla, T), use of phased array head coils, and image (post)processing and analyses [9, 14]. Currently, the clinical state-of-the-art imaging for lesion detection in epilepsy includes a 3-T MRI dedicated epilepsy protocol, reviewed by an experienced neuroradiologist in the field of epilepsy(surgery) [15]. However, even under these optimal circumstances, small structural abnormalities, like focal cortical dysplasias (FCD), can remain unidentified at 3 T [16, 17]. FCDs are congenital malformations of cortical development characterized by aberrant migration and differentiation of neuronal cells [18, 19] and are a major cause of chronic epilepsy, especially in children [20]. It has been reported that FCD is the most frequent lesion (45–51%) in epilepsy surgery candidates who are “MRI-negative” at 3 T [17, 21], and cannot be visualized in up to 40% of the cases [22].

We hypothesize that UHF MRI (7 T and 9.4 T) leads to improved detection and quantification of tiny structural and functional (sub)cortical abnormalities, due to a higher spatial resolution and contrast level beyond what is available at 3 T [23, 24]. By applying 9.4 T, we hypothesize that there will be an additional diagnostic gain compared to 7 T MRI. Additionally, this increased lesion detection of UHF MRI, and additional voxel-based morphometry postprocessing techniques of the UHF images, will guide surgical decision-making, leading to a more personalized type of epilepsy surgery and improved postoperative seizure outcome, with a higher chance of becoming seizure free in potential candidates for epilepsy surgery.

The primary objectives of this study are (1) to estimate the detection rate of structural and functional brain lesions on 7 T and 9.4 T MRI in patients with drug-resistant 3 T MRI-negative focal epilepsy and (2) to assess whether this increased detection rate is associated with improved postoperative seizure outcome. In this paper, we present the study protocol according to Standard Protocol Items: Recommendations for Interventional Trials protocol guidelines [25].

## Methods and analysis

### Study setting and population

This is a multicenter prospective, longitudinal, therapeutic study assessing the value of UHF MRI for lesion detection and therapeutic impact of this improved lesion detection, in patients with a suspected focal cause of drug-resistant epilepsy and unrevealing clinical 3 T MRI, who are candidates for resective epilepsy surgery (Fig. 1).

**Fig. 1 Fig1:**
[figure not shown]
Study participants’ timeline

The diagnosis of focal epilepsy and a suspected region of interest (ROI) as the focal epileptogenic zone is based on thorough examinations including medical history with seizure semiology, a video-EEG, neuropsychological examination, and 3 T MRI according to a dedicated epilepsy protocol [15, 26], including morphometric analysis program (MAP18) postprocessing [27, 28]. In selected cases, a PET scan and/or subtraction ictal SPECT co-registered to MRI (SISCOM) and/or EEG triggered fMRI and/or MEG are performed. In a subset of these patients, with discordant results from non-invasive examinations, intracranial EEG recordings by implanted surface or intracerebral depth electrodes are necessary. Subsequently, a multidisciplinary team, consisting of neurosurgeons, neurologists, clinical neurophysiologists, neuropsychologists, and neuroradiologists, assesses eligibility for epilepsy surgery. All clinical 3 T MRI scans are reviewed by a radiologist specialized in epilepsy imaging, and are considered “negative” only after review of the scan in the multidisciplinary team, where the 3 T scan and other non-invasive examination are considered.

### Inclusion and exclusion criteria

For the present study, we include pediatric patients (children, aged 12–17 years) and adults (aged 18 and above), with drug-resistant focal epilepsy (ongoing seizures despite at least two adequate and well-tolerated anti-epileptic drugs trials [29]), who are under evaluation for resective epilepsy surgery. All patients have had a clinical 3 T MRI without an identified explanatory epileptogenic lesion. Exclusion criteria are intellectual disability (IQ < 70), incapacity to sign informed consent, pregnancy, and criteria specific for UHF MRI (see Table 1).

**Table 1 Tab1:** Overview of inclusion and exclusion criteria

Inclusion criteria
Age ≥ 12 years
Drug-resistant focal epilepsy
Work-up for epilepsy surgery
Clear suspicion on the focal onset of the epilepsy
Absent explanatory abnormalities on conventional 3 T MRI
Informed consent signed
Exclusion criteria
Incapacitated to sign informed consent
Patients and/or legal representative have an intellectual disability (IQ < 70)
Pregnancy
MRI-exclusion criteria:
Claustrophobia
Pacemaker, neurostimulor, insulin pump or other pump
Aneurysm clips in cerebro not safe at 7 or 9.4 T MRI
Metal particles in the head (incl. eye)
Hearing prostheses (not all types)
Tattoos above the diaphragm
Other body implants not proven safe at 7 or 9.4 T MRI
Relative contra-indications depending on place and kind
Artificial heart valves
Joint prostheses
Obesity making MRI-scanning impossible due to size

### MRI-protocol

MRI acquisition will be performed at Scannexus BV, a specialized UHF MRI research facility, using an actively shielded Siemens Magnetom “classic” 7 T with whole-body gradients and 32-channel NOVA head coil, and a Siemens Magnetom 9.4 T with head-gradient set and 31-channel receive/16-channel parallel RF transmit head coil.

Development of a clinically applicable 7 T and 9.4 T MRI scan protocol for detection of structural abnormalities is part of this study. We created a format for a proposed UHF scan protocol (see Table 2). All sequences will acquire images of the whole brain. This scan protocol allows for the use of normative control data, acquired by Haast et al. [30]. Two dielectric CaTiO_3_ pads with demineralized water are used to improve the inhomogeneous MRI signal in the temporal lobes. As a preparation, we scanned some controls at 7 T to assess image quality (see Figs. 2 and 3).

**Table 2 Tab2:** Proposed UHF MRI scan protocol, consisting of 3D T1-MP2RAGE (magnetization prepared two rapid gradient echoes), 3D SPACE FLAIR (fluid-attenuated inversion recovery), 2D T2-SPACE, 2D dual-echo GRE (spoiled-gradient echo), 3D GRE ASPIRE, BOLD (blood-oxygen-level-dependent) resting-stage functional MRI, DTI (diffusion tensor imaging), ASL FAIR (arterial spin labeling flow-sensitive alternating inversion recovery), and total acquisition time ± 70 min

	Type	Sequence	Aimed voxel size (mm)
-	Localizer		1.1 × 1.0 × 3.0
-	B0 map		2.9 × 2.9 × 4.0
-	B1 map		3.9 × 3.9 × 5.0
1	Structural	3D T1-MP2RAGE	0.7 × 0.7 × 0.7
2		3D FLAIR	0.8 × 0.8 × 0.8
3		2D T2-SPACE	0.6 × 0.6 × 2.0
4		2D dual-echo GRE	0.3 × 0.3 × 2.0
5		3D GRE ASPIRE	0.7 × 0.7 × 0.7
6	Functional BOLD	BOLD rs-fMRI	1.4 × 1.4 × 1.4
7	Diffusion	DTI	1.05 × 1.05 × 1.05
8	Functional ASL	ASL FAIR	2.8 × 2.8 × 2.8

**Fig. 2 Fig2:**
[figure not shown]
7 T 3D T1-MP2RAGE axial image of a test subject’s cerebrum with an isotropic voxel size of 0.7 mm. The di-electric pads can be seen on both sides

**Fig. 3 Fig3:**
[figure not shown]
7 T 2D dual-echo GRE (T2*) axial image of a test subject’s cerebrum with a voxel size of 0.3 × 0.3 × 2.0 mm

### Intervention and evaluation protocol

Patients are included after obtaining written informed consent; subsequently, MRI will be performed. In a first run, both 3 T and UHF images will be independently evaluated by two neuroradiologists experienced in epilepsy-imaging, and a neurosurgeon or neurologist specialized in epilepsy surgery, without prior knowledge of previously obtained non-invasive examinations and the potential epileptogenic zone (= ROI). In a second run, first the 3 T, subsequently, the UHF MRI scans will be evaluated with prior knowledge of the ROI by the same investigators. The images will be reviewed for image quality and potential epileptogenic lesions using a structured UHF MRI scoring form, allowing objective comparison between observers and scans. Lesion size/volume, number, lateralization, localization, shape, and signal intensity detected on the different sequences are marked. The mesiotemporal structures (hippocampus, amygdala) are evaluated for abnormalities and asymmetries in volume and signal intensity. Evaluation for FCDs is done by screening for features of blurring cortical-subcortical junction/cortical thickening/transmantle sign/hyperintensity of grey and white matter/abnormal gyral-sulcal pattern/segmental or lobar hypoplasia/hypoplasia with loss of regional white matter volume. Additionally, we evaluate features of an intracortical black line as a possible marker of a FCD and magnetic susceptibility effects due to tissue irregularities [31]. Additionally, susceptibility effects are used to detect the presence of abnormal vasculature adjacent to areas of cortical dysplasia or polymicrogyria [32]. A diffusion sequence (by acquiring diffusion tensor imaging, DTI) is firstly performed to aid the detection of intra-cortical radial and tangential diffusion abnormalities, suggestive for FCD types 1a and 1b, and secondly to detect a difference in intra-cortical radial and tangential diffusion between FCD types 1a and 1b. Using post-processing, additional FA and ADC maps will be generated. Abnormalities in blood-oxygenation level fluctuations are detected using resting-state fMRI and arterial spin labeling (ASL). Furthermore, we will make use of voxel-based morphometry (VBM) structural post-processing technique. The aim of this technique is to quantitatively analyze morphology and signal intensity on both 3 T and UHF scans by using algorithms for automated FCD detection as qualitative visual inspection of the MRI will fail to detect tiny aberrances [33].

Results of the UHF MRI scans will be presented and discussed in a monthly multidisciplinary epilepsy surgery conference. We will evaluate the association between the presence and absence of an abnormal finding, with information of other non-invasive examinations. Additionally, we will assess the potential improvement in detection rate after adding prior knowledge of the ROI to the results of reviewing, by comparing the first with the second run, along with intra-observer and inter-observer variability.

After obtaining UHF MRI results, patients can undergo either (1) resective epilepsy surgery, (2) implantation of intracerebral depth electrodes for intracranial EEG recordings (S-EEG), (3) S-EEG guided radiofrequency thermo coagulation (RFTC), or (4) proceed to palliative treatment options (e.g., vagus nerve stimulation). Surgical resection is the first choice due to its efficacy and will be performed when possible, with regard to lesion location, extent, and expected lesion etiology. Depth electrode implantation will be used when additional information on the possible epileptogenic zone is required. S-EEG RFTC will be performed when resective surgery is not recommended, for example, in case of deep-seated periventricular heterotopias. Palliative treatment options are explored when other curative treatments are excluded. Samples of surgically treated patients will be examined by routine histopathological analysis and classified according to ILAE guidelines [20]. In case of resective epilepsy surgery, UHF MRI–based diagnosis will be compared to histopathological diagnosis. Postoperative seizure outcome following ILAE and Engel classification [34] will be assessed by the treating neurologist as standard care minimally 1 year after surgery.

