### Outcome parameters

The primary outcome parameter of this study is the number of patients with detected “epileptogenic” structural and functional brain abnormalities on 7 T and 9.4 T UHF neuroimaging, the so-called “diagnostic gain” in patients with 3 T MRI-negative drug-resistant focal epilepsy. The second primary outcome parameter is postoperative seizure outcome (ILAE/Engel class at 12 months) in operated UHF MRI-positive versus MRI-negative patients “i.e., therapeutic gain.”

As secondary outcome parameters, detection rate of UHF resting-state fMRI for cortical abnormalities in spontaneous blood oxygenation level-dependent (BOLD) signal fluctuations as a marker of an epileptogenic lesion, concordance of UHF MRI imaging with histopathological diagnosis of surgical specimen, intra- and inter-observer agreement for UHF MRI evaluation, and association between ROIs in the non- or semi-invasive work-up modalities and UHF MRI data will be assessed.

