### Statistical analysis

Baseline characteristics of the cohort will be described in detail as mean and standard deviation or median and interquartile range for continuous variables (depending on their normality of distribution) and as count and percentage for categorical variables. Missing values are unlikely to occur, but in case of incomplete MRI data, we will use stochastic regression imputation to facilitate the inclusion of all study participants in the analyses.

UHF MRI data, such as characteristics of and, if applicable, localization of abnormalities, will be summarized using descriptive statistics. Primary outcomes diagnostic and therapeutic gain will be expressed as point estimates with 95% confidence intervals. Explorative analysis is used for quantitative MRI measurements (diffusion, fMRI, ASL). Radiological assessment will be done independently, in case of different results consensus will be sought. Intra-observer and inter-observer agreement in assessing MRI images will be quantified using Cohen’s kappa for categorical MRI parameters, and intra-class correlation coefficient (ICC) for continuous MRI parameters. Associations between qualitative findings and histopathological abnormalities will be computed using Spearman rank correlation, point bi-serial correlation, or Fisher’s Exact test, depending on the distribution of the findings.

We will assess the association between demographic, clinical parameters, and outcome measures by using univariable and multivariable regression analysis. A *p*-value of < 0.05 will be considered statistically significant. Statistical analysis will be performed using IBM SPSS software version 25 or higher.

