### Challenges

Sample size calculation for a study assessing diagnostic gain and improvement of postoperative seizure outcome is not trivial as there is no comparable research based on other modalities (SPECT, PET, etc.). Thus, no power calculation based on prior studies can be performed. Therefore, we took a pragmatic approach with sample size calculation based on observations needed for each variable entered in a regression model. Final study power has to be established.

The main technical challenges for UHF MRI acquisition are inhomogeneities in the main magnetic field (*B*_0_) and radiofrequency transmit field (*B*_1_) and their stronger interaction with any implants. The current proposed scan protocol might lead to increased sensitivity to motion artifacts due to longer scanning times in the chosen highest resolution protocols, as the patient has to lie still for a longer period of time. Our total scan time of ± 70 min is slightly above acquisition times of other 7 T studies, where acquisition time was not an issue [23, 31, 35, 47]. Additionally, clinical 3 T MRI is performed at an earlier stage than UHF MRI in the epilepsy surgery workup. The results of additional examinations possibly lead to novel insights on the ROI, influencing reviewing of UHF MRI scans. A potential bias may occur because not all patients receive all other non-invasive examinations, but at the clinician’s discretion. Furthermore, inexperience in clinical reading/interpretation of 7 T and 9.4 T images can be an issue, as reviewers might experience a reviewing learning curve. Also, UHF might produce artifacts or geometric disturbances not seen on conventional MRI, potentially resulting in detection of non-relevant lesions (false positives). To address this issue, several UHF pilot scans will be performed to gain experience at reviewing UHF MRI. This includes patients with positive 3 T MRI for a small lesion, along with non-epileptic volunteers.

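### As described, the only repeat reading by the same reader changes what the reader knows, so agreement between the two runs is not intra-observer repeatability

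*Protocol article*

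**What the plan says.** All references are to the Protocol article.

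- **Intervention and evaluation protocol.** In run 1, two neuroradiologists and a neurosurgeon or neurologist read the 3 T and UHF images independently, unaware of the other examinations and of the suspected zone. In run 2, "first the 3 T, subsequently, the UHF MRI scans will be evaluated with prior knowledge of the ROI by the same investigators". The order is fixed: blind first, informed second.
- **Same section.** The improvement in detection from knowing the ROI is assessed "by comparing the first with the second run, along with intra-observer and inter-observer variability".
- **Outcome parameters.** One secondary outcome is "intra- and inter-observer agreement for UHF MRI evaluation".
- **Statistical analysis.** "Intra-observer and inter-observer agreement in assessing MRI images will be quantified using" Cohen's kappa for categorical parameters and the ICC for continuous ones. The pair of readings behind the intra-observer figure is not named.
- **Challenges.** The authors note that "reviewers might experience a reviewing learning curve". Pilot scans are planned so that readers gain experience; measuring repeatability is not given as their purpose.

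**The concern.** Intra-observer agreement asks whether a reader gives the same answer twice when nothing but the occasion has changed. In the scheme described, the only two reads by one reader differ on purpose in what the reader has been told.

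The plan's own hypothesis makes this matter. The Discussion (Diagnostic value) treats a prior hypothesis about location as crucial for finding subtle lesions. If that is right, readers should change some calls between runs, and kappa falls because the ROI information worked. A reader of the results could then take a low kappa as poor repeatability of UHF reading, for a technique the authors hope to bring into standard pre-surgical work-up.

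The ROI comparison has a separate weakness. Run 2 is always the second look by the same people at the same images, so any systematic effect of looking again falls on the ROI-informed run.

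**Working it through.** **Plan figures.** The article gives no figure for agreement, for blind detection or for the ROI gain. Its only design figures are 60 patients, from 10 × (5 + 1) = 60, and a half-width below 0.20 for the detection rate. At a rate of 0.5 the half-width is 1.96 × √(0.25/60) = 0.127. Both figures hold, and neither bears on this point.

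**Step 1: a perfectly repeatable reader.** Assumptions: 19 of 60 scans are positive with the ROI known (19/60 = 0.317, close to the 6/19 = 0.316 cited under Sample size); the number of blind positives, *a*, varies; no positive is reversed. The 2×2 table is then: both positive *a*, positive to negative 0, negative to positive 19 − *a*, both negative 41.

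- Observed agreement: po = (*a* + 41)/60
- Chance agreement: pe = [*a* × 19 + (60 − *a*) × 41]/3600
- kappa = (po − pe)/(1 − pe)

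| Blind positives | po | pe | kappa |
|---|---|---|---|
| 6 | 47/60 = 0.783 | 2328/3600 = 0.647 | 0.39 |
| 9 | 50/60 = 0.833 | 2262/3600 = 0.628 | 0.55 |
| 12 | 53/60 = 0.883 | 2196/3600 = 0.610 | 0.70 |
| 15 | 56/60 = 0.933 | 2130/3600 = 0.592 | 0.84 |
| 18 | 59/60 = 0.983 | 2064/3600 = 0.573 | 0.96 |

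True repeatability is 1.0 in every row.

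**Step 2: can kappa separate the two causes?** Let the blind rate be *p* = 0.20, let *k* be the same-condition kappa, and let ROI knowledge turn a share *g* of second-read negatives positive. Without ROI information, both-positive is A = p² + k·p(1 − p), each discordant cell is B = p − A, and both-negative is D = 1 − A − 2B. With it, the cells become A + gB, B(1 − g), B + gD and D(1 − g).

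| k | g | Observed kappa | Reversals per 60 |
|---|---|---|---|
| 1.0 | 0.20 | 0.615 | 0 |
| 0.8 | 0.10 | 0.626 | 1.7 |
| 0.6 | 0 | 0.600 | 3.8 |

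Three quite different situations give nearly the same kappa, so kappa alone cannot separate them. The count of positive-to-negative reversals differs, but using it to recover *k* requires assuming that ROI knowledge never makes a reader withdraw a finding, for example one outside the ROI.

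**Step 3: the net ROI gain.** In the same model the net change is (B + gD) − B(1 − g) = g(B + D) = g(1 − p), which does not contain *k*. It is 0.10 × 0.80 = +0.08 or 0.20 × 0.80 = +0.16 whether *k* is 1.0, 0.8 or 0.6. Random reader noise does not bias it.

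A systematic order effect does enter. An observed gain of +0.12 fits ROI 0.12 with order 0, ROI 0.06 with order 0.06, or ROI 0 with order 0.12. Two runs in fixed order cannot tell these apart.

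**The case against.** **The article is condensed.** It says that agreement is assessed along with the run comparison, not that it is computed from it, and it does not name the pair of readings. A reader might infer that intra-observer agreement can only come from run 1 versus run 2. That goes too far: a same-condition re-read in the full protocol is not excluded. What remains is that the article sets out its reading scheme in detail, and that scheme contains no suitable pair.

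**The ROI gain survives.** A reader might infer that it is not identified at all, or that reader noise inflates it. Step 3 shows otherwise for random noise. Nor do the documents support saying that the gain is overstated: a second look or learning could raise it, while a reader who remembers and repeats the first answer would shrink it and raise kappa. Blind-then-informed is also the natural order, since knowledge cannot be withdrawn.

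**The size is hypothetical.** This is true. The blind counts are assumptions, and at 18 of 60 the distortion is negligible. Other scored items, such as image quality or mesiotemporal asymmetry, may hardly respond to ROI knowledge.

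**Three readers and Cohen's kappa.** A two-rater statistic might look wrong here, but pairwise use among three readers is acceptable. Inter-observer agreement within a run is unaffected.

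**A small re-read is imprecise.** This also stands. Using SE = √[po(1 − po)/n]/(1 − pe) with n = 15 and an assumed kappa of 0.7, the 95% half-width is about 0.39 at prevalence 0.316 (po 0.870, pe 0.568) and 0.47 at prevalence 0.20 (po 0.904, pe 0.680). The second-look change would be imprecise too. The re-read would still estimate the intended quantity, which the run comparison does not.

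**Conclusion.** The point holds for the reading scheme as described. A kappa or ICC between run 1 and run 2 measures agreement across two information conditions, and it falls when ROI knowledge changes calls as intended. Under the stated assumptions (19 of 60 positive with the ROI known, no reversals), a perfectly repeatable reader would show 0.39 to 0.96, depending on an unknown blind detection rate.

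The ROI gain can be estimated as a paired difference, but it carries any systematic second-look, recall or learning effect, in a direction the documents do not settle.

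The consequence is confined to one secondary outcome and to the label on the run comparison. No effect on either primary outcome has been shown.

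**What to change.** 1. Do not compute intra-observer agreement from run 1 versus run 2, and name the pair of readings that defines it.
2. Have the existing readers repeat the ROI-blind read on a random subset, re-coded and shuffled, after a washout. Report kappa and ICC from those pairs with confidence intervals, which will be wide with about 15 scans.
3. Use the same pairs to gauge the second-look change, and set it beside the run 1 to run 2 change.
4. If no re-read is done, drop the intra-observer outcome, or report the run 1 to run 2 figure as agreement across information conditions.
5. In either case, label the run comparison as ROI knowledge plus second reading.

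Cost: with 15 scans and three readers, 15 × 3 = 45 extra readings, and no new reader, patient or scan. Without the re-read, the cost is a narrower claim.
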